## 3. Outcomes

The assessments will be carried out in the laboratory of the Faculty of Sport Sciences and Physical Education—University of Coimbra. The space is ample and isolated, the temperature controlled, and each step of the assessment should be organized to provide maximum comfort and privacy to each participant. The research team will provide information on the procedures and aims. The researchers will answer any questions that may arise. All assessments will be performed in a controlled environment, during the morning period, with only the ingestion of breakfast due to the characteristics of the participants and the taking of medications.

## 4. Instruments/Procedures

### 4.1. Anthropometry

For the measurement of body mass and height, a scale with a portable stadiometer model seca (model 870, Hamburg, Germany) will be used. The participant will stand barefoot on top of the stadiometer platform, leaning against the pole of the device, looking forward, and with arms along the body. Subsequently, the Body Mass Index of the formula, weight (kg)/height (m^2^) will be calculated and the waist circumference will be measured, measured halfway between the iliac crest and tenth rib, directly on the skin, using a flexible tape measure; the methods being viable, reliable, and accurate for the population [37].

### 4.2. Body Composition

For the evaluation of body composition, bio-impedance equipment (InBody770) will be used, being a viable, reliable, and non-invasive method [38]. The participant must climb to the platform of the device with bare feet, to contact the four electrodes of the feet, measure the weight, and hold the bar with the four electrodes of the hands.

### 4.3. Neuromuscular Capacity

Lower limb strength will be assessed using an isokinetic dynamometer (BIODEX Multijoint System 3 Pro, Shirley, NY, USA), which is reliable for the target population [39], through leg flexion and extension, using maximal concentric contractions. Equipment calibration was performed before the evaluation session according to the manufacturer’s instructions (Biodex Medical Systems, Inc., 2000, Shirley, NY, USA). Participants will sit in the equipment chair (chair inclined backward at 85° of hip flexion), according to the manual’s recommendations, and stabilize using crossed belts close to the chest, hip, and thigh of the member to be evaluated, in order to avoid compensation. The axis of rotation of the dynamometer was aligned with the external femoral condyle of the knee. The fixing strip of the pad was adjusted 2 cm above the upper edge of the fibular malleolus. The global range of motion was defined as between 85 and 90°. The individual gravity calibration was corrected before each test in the position of 30 degrees of knee flexion [40]. To familiarize the participants, before starting the test, 3 repetitions were performed for each velocity and action [41]. During the test, participants were instructed to keep their arms crossed with their hands on the opposite shoulder. The computer screen connected to the dynamometer provided consistent visual feedback in real time [42]. The warm-up protocol consists of 5 min of walking at a comfortable intensity. Concentric and eccentric reciprocal muscle actions will be tested considering 3 repetitions for each movement 60°.s^−1^ (1.05 rad/s) and 120°.s^−1^ (3.14 rad/s). A 60 s interval was established between the 3 rep familiarization and the test, as well as between angular velocities [43]. Values will be obtained such as peak torque, Peak TQ/BW, Maximum Repetition Total Work, Coeff of Var., Average Power, Total Work, Acceleration Time, Deceleration Time, ROM, Average Peak TQ, and Agonist/antagonist ratio.

To measure upper limb strength, a handgrip test will be used, using a manual dynamometer, the reliability and validity of which have been confirmed by Cabeza-Ruiz et al. [44] and Oppewal and Hilgenkamp [45] and the procedures recommended by the Brockport Fitness Test Manual will be used [46]. The “3 kg medicine ball throw test” will also be applied [47], valid and reliable for people with IDD [37], in order to assess the muscular power of the upper limbs. The participant will be seated in a chair with the ball close to the chest. At the start signal, throw the ball, and raise the chest pass from as far as possible.

The test of 3 maximum repetitions, for the prescribed actions/movements, will also be applied to the participants of the indoor PE program. To perform the test of 3 maximum repetitions for the participants of the IG, a small warm-up is performed, and a load is placed on the equipment, depending on the experience of the PE technician who supervises the test, so that the individual cannot perform more than 3 repetitions. If you exceed 3 repetitions, the load is gradually increased (2–5 kg) and a rest period is given between the new set (3–5 min).

### 4.4. Functional Capacity

Fullerton battery of functional tests [48] will be used to assess physical fitness, namely, the tests: “sit to stand” for 30 s, evaluating the strength and resistance of the lower limbs, a viable and reliable test for people with IDD [37,49]. The purpose of the test is to assess the strength and resistance of the lower limbs (number of executions in 30 s without using the upper limbs). The test begins with the participant sitting in the middle of the chair, with the back straight and feet shoulder-width apart and fully supported on the floor. At the “start” signal, the participant rises to maximum extension (vertical position) and returns to the initial sitting position. The participant is encouraged to complete as many repetitions as possible within a 30 s time interval.

The “agility” test to assess physical mobility, validity, and reliability will be used as assessed by Cabeza-Ruiz et al. [44], in which the objective is to assess physical mobility, namely, speed, agility, and dynamic balance. The participant must be seated in the chair, with hands on thighs and feet flat on the floor. At the starting signal, he gets up from the chair and walks as fast as possible (without running), around a cone (located at 2.44 m) and returns to the chair. The participant must be informed that the test is evaluated by the time it takes to perform the exercise.

The “6 min walk test”, to assess aerobic resistance, is also valid and reliable for the study population [50]. The objective of the 6 min walking test is to assess aerobic resistance by covering the greatest distance in 6 min. At the starting signal, the participant is instructed to walk as quickly as possible (without running) the distance marked around the cones. If necessary, participants can stop and rest, being able to sit down and resume the course.

### 4.5. General Health Status

For the evaluation of the general state of health, blood samples will be collected by professionals accredited for this purpose, through the venipuncture technique [51]. The results will be analyzed by the certified laboratory to which the professional belongs and will be sent via email to the principal investigator of the study.

A digital sphygmomanometer Omron Digital Blood Pressure Monitor HEM-907 (Omron Healthcare Europe BV, Matsusaka, Japan) will be used to obtain hemodynamic parameters, such as resting blood pressure (systolic and diastolic) and resting heart rate, as well as an oximeter. Participants, before data collection, will remain at complete rest for five minutes, with legs uncrossed, and back and arm supported without speaking/or moving [52]. Two readings will be taken, with an interval of 1–2 min between them and the average of these readings will be recorded. If the values deviate ≥ 5 mmHg, a third measurement will be taken [52]. Measurements will be taken in the morning, with only one meal and participants will be instructed to avoid caffeine, exercise, and smoking for at least 30 min before measurements [52].

The Heart Rate Variability will also be evaluated, according to the procedures of Proietti et al. [53] and the guidelines *Task Force of the European Society of Cardiology* and the *North American Society of Pacing and Electrophysiology* [54], using a Polar ProTrainer (Kempele, Finland). Participants will place the sensor on their chest, below the pectoralis major. Afterward, the participants will be instructed to sit comfortably in a chair, with their eyes open, with a calm breath, and to avoid any movement during the data acquisition period. The test will last 10 min, in a calm, silent, and low-light environment. After the test is performed, the data will be downloaded via the Polar Flow Web Service as “.txt” files and exported for analysis using the Kubios HRV software package (Kubios HRV, Biomedical Signal Analysis Group, Department of Applied Physics, University of Kuopio, Finland) [55]. The RR intervals corresponding to the first two minutes will be discarded (stabilization period) and the data from the following five minutes will be used to calculate the heart rate variability. In the time domain, the following items will be calculated: (i) mean RR (mean of the RR intervals in ms); (ii) SDNN (standard deviation of RR intervals in ms); (iii) RMSSD (root mean square of successive RR interval differences in ms); (iv) pNN50 (percentage of successive RR intervals that differ by more than 50 ms). In the frequency domain, the following items will be calculated: (i) LF (absolute power of the low-frequency band, 0.04–0.15 Hz, in ms2); (ii) HF (absolute power of the high-frequency band, 0.15–0.4 Hz, in ms2; (iii) ratio of LF-to-HF power (LF/HF).

### 4.6. Quality of Life

For the evaluation of QoL in people with IDD, the *Personal Outcomes Scale* [56,57], in the Portuguese version [58] based on the model of Schalock and Verdugo [59], developed at the *Arduin Foundation and Ghent University*, will be applied by technicians with specific training for this purpose.

The Personal Outcomes Scale includes eight domains, each containing five questions, which can be answered through self-report or the report of caregivers, who may be family members or professionals, making a total of forty questions, presented with three response options, through the Likert format, as, for example, often, sometimes, or never, thus making it possible to (1) measure the results of service interventions; (2) reorient public policies to improve these results; (3) improve support management and the service financing mechanism; (4) compare to QoL of citizens; (5) monitoring the application of human and legal rights, provides crucial information so that it can be used to improve the quality of intervention and credible and sustainable practices, important to implement strategies that align at different levels of systems [58].

### 4.7. Cognitive Function

The *Mini-Mental State Examination* is a simple test, using a sheet of paper and pencil, with an easy and quick application (about 5 to 10 min) [60] and is a cognitive deficit/dementia screening test. This test is adapted to the Portuguese population [61], has been applied by some authors to the population with IDD [62], and consists of thirty items (scored with a value of 0—when the person gives an incorrect answer or simply does not answer or 1—when the person answers correctly) organized by six domains: Orientation (which assesses recent memory, attention, and the temporal–spatial orientation); Retention (assess attention and short-term or primary memory); Attention and Calculation (assesses calculation ability, attention, and immediate and working memory); Evocation (assesses recent or secondary memory); Language (assesses spontaneous speech, listening, repetition, naming, reading, and writing). The maximum test score is thirty points, with higher scores indicating better results.

To assess cognitive ability through the *Mini-Mental State Examination*, you will need a sheet of paper and pencil. The test will take about 5 to 10 min and will be conducted by a technician with specific training for this purpose, following the protocol. As with the Personal Outcomes Scale, the application of the Mini-Mental State Examination scale will be carried out in a room without isolation from noise and possible distractions, in a 1:1 aspect (one specialist for one participant).

For the evaluation of QoL in people with IDD, the *Personal Outcomes Scale* will be applied to the self and to the reference technicians/caregivers, by specialists with specific training for this purpose, following the protocol. The application of the scale will be carried out in a room without isolation from noise and possible distractions, in a 1:1 aspect (one specialist for one participant).

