Despite the importance of PA and/or PE benefits, this population has high rates of sedentarism and low levels of physical activity engagement [16,17], not meeting the recommendations [18,19], which puts them at greater risk of developing chronic diseases [20] and consequent premature death [21,22]. The risks of physical inactivity in people with disabilities increase when compared to the general population: higher prevalence of hypertension (25 to 41% compared to 29% in the general population); obesity (30.8 to 36.6% compared to 18.2 to 18.5%); and metabolic syndrome (21 to 29.3% compared to 13.5% to 17.9%) [23,24]. In addition, as the degree of disability increases, physical activity levels decrease more significantly [25], affecting their physical fitness, capacity to perform activities of daily living, and independence [26]. To promote their life conditions, people with IDD should be integrated into PA and PE practice, according to recent recommendations [18,19].

One of the possible reasons for these low levels of practice is the existence of barriers that hinder their practice. Among them, we can find factors such as financial cost and lack of adapted PE [27,28]. To reduce the impact of these barriers, it is important to develop PEs. Besides being adapted to the individuals, they must be accessible to any type of context and financial availability, both for the individuals and the support institutions. In addition, the development of these PE may contribute to the reduction in the risk of the onset of metabolic and cardiovascular diseases, which decreases healthcare costs and promotes physical fitness, functionality, and QoL. Therefore, the main objective of the present study is to evaluate and compare the effectiveness of two different 24-week PE programs on levels of physical fitness, general health, dementia/cognitive decline, and QoL in individuals with IDD.

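### Section 4.7 places the cognitive test and the quality-of-life interview in a room not isolated from noise, in conflict with the isolated, controlled setting that Section 3 gives for all assessments

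*Protocol article*

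**What the plan says.** Section 3 (Outcomes) sets the general conditions of measurement. On place: "The assessments will be carried out in the laboratory of the Faculty of Sport Sciences and Physical Education". On the room: "The space is ample and isolated, the temperature controlled". On scope: "All assessments will be performed in a controlled environment, during the morning period". It also asks that each step give participants comfort and privacy. No instrument is exempted.

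Section 4.7 (Cognitive Function) sets the conditions for two instruments. For the cognitive test: "the application of the Mini-Mental State Examination scale will be carried out in a room without isolation from noise and possible distractions". For the Personal Outcomes Scale, in a separate sentence: "The application of the scale will be carried out in a room without isolation from noise and possible distractions". Both sentences add that testing is one specialist to one participant.

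The main objective in the Introduction is to compare the two programs "on levels of physical fitness, general health, dementia/cognitive decline, and QoL in individuals with IDD". The Mini-Mental State Examination (MMSE) is the only instrument described for cognition, and the Personal Outcomes Scale the only one for quality of life (QoL).

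**The concern.** An assessor who follows Section 4.7 to the letter would test in a room open to noise and interruption. An assessor who follows Section 3 would use an isolated, controlled space. The article does not say which governs.

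The setting matters most for the MMSE. By the article's own description, one of its domains is "Attention and Calculation (assesses calculation ability, attention, and immediate and working memory", and others score short-term and recent memory. Distraction plausibly disturbs these functions, and the participants have mild to severe intellectual disability.

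At stake are hypotheses iii and vii (cognition) and iv and viii (QoL). The sample is 21 people in three groups at 1:1 allocation, nominally 21/3 = 7 per group, so there is little precision to spare. Scores collected at week 0 under poor conditions cannot be repaired later.

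**Working it through.** The article states no figure on this point, so the check is a comparison of text followed by reasoning on what the literal instruction would do.

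**1. The statements side by side**

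| Item | Section 3, all assessments | Section 4.7, MMSE and Personal Outcomes Scale |
|---|---|---|
| Place | One university laboratory | A room, not further identified |
| Isolation | Space described as isolated | Not isolated from noise or distractions |
| Control | Controlled environment for all assessments | Distractions treated as possible |
| Exceptions | None named | No reference to Section 3 |

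Both Section 4.7 sentences are complete and grammatical, so this is not a text-extraction fault. It is also not detail left out by a condensed article: a condition is stated, and it disagrees with another stated condition.

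**2. Outcomes touched**

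The main objective names four domains: physical fitness, general health, cognitive decline and QoL. The two instruments cover the last two, so 2 of 4 domains are affected.

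**3. Effect of the literal instruction on the comparisons**

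Let σ be the between-person SD, r the correlation between visits, σₑ the SD of the added error (independent at each visit), and b₀, b₁₂, b₂₄ the average effect of room conditions at each visit.

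- *Comparison between times (Wilcoxon or Friedman, Section 8).* The variance of a change score goes from 2σ²(1 − r) to 2σ²(1 − r) + 2σₑ². The inflation factor is 1 + (σₑ/σ)²/(1 − r). This is lost precision.
- *Mean shift between times.* The average change from week 0 to week 24 is displaced by b₂₄ − b₀. This is zero if conditions are the same at both visits and non-zero only if they differ.
- *Comparison between groups (Kruskal–Wallis, Section 8).* The stated room condition is the same for all three groups. A common b at a visit cancels between groups, which leaves only the added spread.

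The planned tests use ranks, so the variance factor gives the direction of the loss and not its exact size.

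**4. Can the size be computed?**

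No. The factor needs σₑ/σ and r. The article gives no SD, reliability or between-visit correlation for either scale, and nothing on the noise level of the room. Any percentage loss or effective sample size would rest wholly on an assumed value.

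**The case against.** The strongest reply is that this is a slip of language. The phrase is tied to one-to-one testing by a trained specialist, a measure that limits distraction, and Section 3 promises privacy and control. The article reverses its sense elsewhere: hypotheses iii and iv in the Introduction are worded as an increase in cognitive decline and in QoL decline after exercise. The repetition is weak confirmation of intent, since the MMSE sentence itself refers to the Personal Outcomes Scale and both repeat one phrase. This stands as a likely explanation. It does not remove the point, because nothing in the article corrects the wording and staff are told to follow the protocol.

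A second reply is that isolated in Section 3 may mean separate and private, not shielded from sound. Section 4.5 (General Health Status) asks for silence separately for heart rate variability, which suggests that silence is not implied by the general setting. This stands in part: strict impossibility of meeting both sections is not shown. Accepting possible distractions still sits badly with a controlled environment for every assessment.

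Three stronger readings are tempting, and the documents do not support them.

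- *The two outcomes are degraded.* The article holds no data on this. Added error is an inference from the literal wording.
- *Noise will bias the group comparison or imitate an exercise effect.* The stated condition is the same for all groups. The same team assesses at each visit, and evaluators other than the principal researcher are kept unaware of group (Sections 2.5 and 5). A false change over time needs conditions to differ by visit, and nothing says that they will.
- *Quality of life is affected as much as cognition.* The Personal Outcomes Scale is also completed by technicians or caregivers, so part of that outcome does not depend on the participant's attention.

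**Conclusion.** The conflict is real and unreconciled. The two sentences in Section 4.7 disagree with the general rule in Section 3 on the conditions under which the cognitive and QoL instruments are applied. Whether the wording is a slip or deliberate, it needs correcting.

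Followed as written, the expected consequence is avoidable random error in the only instruments described for two of the four outcome domains, and so weaker comparisons in a small sample. A shift between visits follows only if room conditions differ between weeks 0, 12 and 24. The size cannot be derived from the article.

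The conclusion rests on two assumptions: that assessors would follow the literal text, and that noise and interruption disturb performance on a test that scores attention and memory. The point affects no sample size, allocation, endpoint or planned test. It should be settled before the baseline assessment.

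**What to change.** Change both sentences in Section 4.7, for the MMSE and for the Personal Outcomes Scale, so that each instrument is applied in a quiet room isolated from noise and distractions, one specialist to one participant, with the same room conditions at weeks 0, 12 and 24. Refer to the space already described in Section 3 so that the two sections agree.

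The cost is two sentences. No visit, equipment or analysis is added, because Section 3 already plans an isolated laboratory space.

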## 5. Procedures

Intervention study that involves several phases: (a) design of PE programs; (b) promotion of the program (information pamphlets will be distributed to the target people with IDD/guardians/tutors/caregivers about the study procedures and aims); (c) sample recruitment (participants/parents/tutors will sign an informed consent form and all project will be carried out in accordance with the Declaration of Helsinki; (d) division according to their intention to participate in the study: (i) IG/indoor context (using weight machines), (ii) OG (low cost), or (iii) CG (no specific intervention; continue with normal daily activities); (e) initial evaluation of the groups by an evaluator blinded to the group belonging; (f) intermidiate evaluation of the groups by an evaluator blinded to the group belonging; (g) final evaluation of the groups by an evaluator blinded to the group belonging; (h) data analysis: descriptive, comparison between groups and conditions, comparison before and after, correlations, among others (subjects who do not perform at least 75% of the sessions will be excluded from data processing).

## 6. Adverse Events

Despite all safety procedures adopted/provided, participants may, at some moment, experience some adverse effects, as well as be aware of some unlikely risks, during the assessment protocols or even during the interventions. When starting a PE program, people who, as a rule, adopt a sedentary lifestyle, run the risk of experiencing some type of discomfort, fatigue, or muscle pain. Given that the intensity will be gradually increased, it is expected that muscle pain will be light and brief, mitigating with the muscle’s habit of exertion. Therefore, the leader will be available for any dialogue throughout the project, to help and advise the participants.

Likewise, participants who develop any type of physical injury or other health problem during the interventions will be referred to the institutional physiotherapy office or family doctor and their continuation in the project will depend on the consideration of all related parties. All adverse physical and psychological outcomes will be recorded, described, and reported in future publications.

